### **3.3 Site approval**

It is expected the site will submit the trial documentation for local research and development approval promptly, and at the latest 6 weeks following ethics approval. The site should begin trial-related screening activities no later than 4 weeks following the receipt of all necessary trial approvals and documentation.

A site initiation meeting with the MRC must occur before a site can be approved to randomise patients. The following documentation should be forwarded to the MRC CTU:

- Patient information sheet and informed consent form on local headed paper
- CV for Principal Investigator and co-investigators.
- Delegation of Authority log.
- Copy of local pharmacy dispensing SOP.
- Approval of the institution's local Research and Development office, if required.

For each clinical trial site, the responsibilities must be documented on the Delegation of Authority log and the contact details (phone, fax and email address) of each person working on the trial must be documented on the Site Information Form. Clinical trial sites must notify the MRC CTU of any subsequent changes to trial personnel and/or their responsibilities. A current copy of the log must be stored in the trial master file at the clinical trial site and also at the MRC CTU.

## 4. SELECTION OF PATIENTS

Patients will be considered eligible for enrolment in the trial if they fulfil all of the inclusion criteria and none of the exclusion criteria defined below.

### 4.1 Patient inclusion criteria

1. Documented HIV infection on ELISA and confirmatory test.
2. Male or female patients, aged 18 years or more.
3. Receiving combination ART for at least 24 weeks with a regimen comprising 2 NRTIs and either an NNRTI or a PI (boosted or un-boosted).
4. No change in ART drugs in the 12 weeks prior to screening.
5. Plasma VL <50 copies/ml at screening and for at least 24 weeks prior to screening (must have at least 1 documented result <50 copies/ml at more than 24 weeks prior to screening, and at least 1 documented result <50 copies/ml taken within 24 weeks prior to screening). A patient who has had one VL "blip" to <200 copies/ml in the 24 weeks prior to screening may be included, provided that the 2 VL tests that immediately preceded the blip and all VL tests (of which there must be at least 1 prior to screening) that immediately followed the blip all gave results <50 copies/ml.
6. CD4+ count >100 cells/mm^3 at screening.  
*This criterion is included because immune reconstitution is a priority in patients with very low CD4+ counts, and there is currently insufficient data to assess whether PI monotherapy will lead to equivalent rates of CD4+ recovery as standard-of-care treatment.*
7. Willing to continue unchanged or to modify, antiretroviral therapy, in accordance with the randomised assignment.
8. Likely to be resident in the UK for the full duration of the trial and willing to comply with trial visit schedule throughout the follow-up period.
9. Willing to provide written informed consent.

### 4.2 Patient exclusion criteria

1. Known major protease resistance mutation(s) documented on prior resistance testing if performed (prior resistance testing is not mandatory for trial participation).
2. Previous change in ART drug regimen for reasons of unsatisfactory virological response (patients who have changed regimen for prevention or management of toxicity or to improve regimen convenience are permitted to enter the trial).
3. Previous allergic reaction to a PI.
4. Patient currently using or likely to require use of concomitant medication with known interaction with PIs including rifampicin, amiodarone, flecainide, bupropion, clozapine,

ergotamine, mexilitine, midazolam, pethidine, pimozide, quinidine, sertindole, sildenafil, voriconazole, zolpidem, St John's Wort.

5. Patient requiring treatment with radiotherapy, cytotoxic chemotherapy, or is anticipated to need these during the trial period.
6. Treatment for acute opportunistic infection within 3 months prior to trial screening.
7. Pregnant or trying to become pregnant at the time of trial entry.
8. History of active substance abuse or psychiatric illness that, in the opinion of the investigator, would preclude compliance with the protocol, dosing schedule or assessments.
9. History of HIV encephalopathy with current deficit  $>1$  in any domain of the Neuropsychiatric AIDS Rating Scale (see Appendix 7).
10. Past or current history of cardiovascular disease, or 10 year absolute coronary heart disease risk of  $>30\%$ , or risk of  $>20\%$  if the patient has diabetes or a family history of premature ischaemic heart disease or stroke (based on the Framingham equation (19), and assessed using the Joint British Societies cardiovascular risk prediction charts, Appendix 10).
11. History of insulin-dependent diabetes mellitus.
12. Patient currently receiving interferon therapy for Hepatitis C virus infection or planning to start treatment for Hepatitis C at the time of trial entry.
13. Co-infection with hepatitis B, defined as Hepatitis BsAg positive at screening or at any time since HIV diagnosis, unless the patient has had a documented Hepatitis B DNA measurement of less than 1000 copies/ml taken whilst off Hepatitis B active drugs.  
*This criterion is included to avoid the risk of a flare of Hepatitis B with NRTI withdrawal.*
14. Any other active clinically significant condition, or findings during screening medical history or examination, or abnormality on screening laboratory blood tests that would, in the opinion of the investigator, compromise the patient's safety or outcome in the trial.
15. Fasting plasma glucose  $>7.0\text{mmol/L}$  at trial screening.

## 4.3 Screening procedures and pre-randomisation investigations

### 4.3.1 Pre-screening check

Prior to the screening visit, a check of medical and drug history should be performed to ensure that the patient meets the basic medical eligibility criteria. Patients will be given adequate information about the trial together with a Patient Information Sheet (see Appendix 1) and given an opportunity to ask questions about the trial.

### 4.3.2 Screening visit

Potentially eligible individuals should be screened between 1 and 4 weeks before trial entry (see section 5.1 for further details regarding scheduling of randomisation visit). The screening visit will be scheduled to occur in the morning due to the need for fasting blood tests. Patients should be instructed to not eat or drink anything (except plain water) from midnight before the visit, although they may take any necessary routine medication. In the event that the patient has not fasted at the screening visit, the glucose and cholesterol

measurement will be omitted and they will be asked to return within 1 week in the fasted state for these tests to be performed. If the patient appears to meet all criteria, but did not have a VL test performed within the 24 weeks prior to screening, a VL done on the screening day can be accepted in lieu of the test in the previous 24 weeks. However, the patient must be recalled for an additional VL prior to randomisation as confirmation of the screening result, and the result of this test must be available prior to randomisation (both tests must show a VL result of < 50 copies).

At the screening visit patients will be asked to verify that they have read the Patient Information Sheet and will be given a further opportunity to ask questions about the trial. If the patient is willing to proceed, the patient and Investigator must both sign 3 copies of the main trial Consent Form (see Appendix 2) (one copy to be given to the patient, one copy for the patient's clinic notes and one copy for the trial file) before any trial-specific screening procedures are carried out. All individuals screened must have their name, date of birth and clinic number recorded in the Trial Register against the next available trial number. This will then become their allocated trial number. The Trial Register must be stored by the investigator in a secure place only accessible to appropriate clinic staff. If an individual is not subsequently randomised the reason should be recorded in the register.

Screening assessments will be performed as listed below and as summarised in the trial schedule (see section 1.3):

- Review of medical history (including previous and current clinically important diseases and medications) and recording demographic information
- Review of symptoms
- Physical examination (including measurement of blood pressure)
- Assessment of cardiovascular risk factors and estimation of 10 year absolute coronary heart disease risk using the Joint British Societies cardiovascular risk prediction charts (see Appendix 11) (19).
- Resting 12-lead electrocardiogram (ECG). The results of an ECG performed during the previous 6 months will be acceptable, provided that the printout is filed and available for review in the patients' case record. The ECG may be performed on or after the day of screening, but results must be available at the randomisation visit.
- Laboratory tests:
  - HIV viral load
  - CD4+ count
  - Full blood count (haemoglobin, white cells, neutrophils, lymphocytes and platelets)
  - Biochemistry (sodium, potassium, urea, creatinine, bilirubin, ALT, alkaline phosphatase)
  - Bone profile (calcium, phosphate)
  - Fasting glucose
  - Fasting lipids (total cholesterol, triglycerides, LDL, HDL)
  - Hepatitis B surface antigen test and hepatitis C antibody test. The results of tests performed during the previous 6 months will be acceptable
  - Plasma storage (2 X 4ml EDTA tube)
  - Urine protein / creatinine ratio
  - Urine storage
  - Urine (or serum) pregnancy test for women of childbearing potential

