| Plasma sample for storage                    | X                           | X                   | X                       |                   | X                    |                                                           | X                                                                                    |
| PI drug concentration                        |                             |                     | X                       | X     | X        |                                                           |                                                                                      |
| Urine protein/creatinine ratio               | X                           |                     |                         |                   | X                    | X                                             | X                                                                                    |
| Urine sample for storage                                 | X                           |                     |                         |                   |                      |                                                           | X                                                                                    |
| Pregnancy test  Urine sample for storage     | X                           |                     |                         |                   |                      |                                                           |                                                                                      |
| Completion of CRF                                        | X                           | X                   | X                       | X                 | X                    | X                                                         | X                                                                                    |

- 1 HIV viral load will be repeated on the same lab sample for any value  $\geq 50$  copies/ml. If  $\geq 50$  copies/ml confirmed on lab re-test, patient will be telephoned for adherence counselling and asked to return for repeat VL test at 4 weeks (window up to 8 weeks) after the first test. Repeat plasma sample for storage will be obtained at the second visit.
- 2 Resistance testing will be performed on a stored sample at the local laboratory in the event of 2 consecutive VL values  $\geq 50$  copies/ml.

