- 3 FBC will include Hb, WCC, neutrophil count, lymphocyte count, platelets; UEC will include sodium, potassium, urea, creatinine; LFTs will include bilirubin, ALT, alkaline phosphatase.
- 4 Bone profile (calcium and phosphate) and urine protein/creatinine ratio will be performed at screening, Week 12 and annual visits in all, but quarterly only in those patients taking tenofovir.
- 5 Lipids will include total cholesterol, triglycerides, LDL, HDL. If elevated at Week 12, additional fasting lipid tests can be performed between the annual visit checks as needed to inform clinical management.
- 6 Blood sample will be stored at screening (2X4ml EDTA), Baseline, Week 12 and annual visits (1X4ml EDTA) plus any visit where a second VL sample is taken for confirmation of rebound (2X4ml EDTA).
- 7 PI drug concentration measurement can be repeated at Week 8 and/or Week 12 if Week 4 concentration is low (only in the PI monotherapy arm).
- 8 Pregnancy test in women only; can be urine or blood test, as per standard practice at site; repeated at any subsequent visits where pregnancy is suspected.
- 9 The final visit will be scheduled within 12 weeks before the common closing date of the trial.

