## 5. RANDOMISATION & ENROLMENT

### 5.1 Randomisation visit (Baseline; Day 0)

If at all possible, the randomisation visit should occur within 4 weeks following the screening visit, but this may be extended to a maximum of 8 weeks for reasons of patient convenience or other operational reasons. The results of all the screening assessments (including ECG) must be available prior to randomisation. There is no requirement for fasting at this trial visit.

For trial entry, all eligibility criteria must be fulfilled. These include the results of the evaluations carried out at screening which must be reviewed prior to the randomisation to make sure that the patient meets the criteria for trial entry. The research team should confirm that the patient continues to consent to enter the trial. The patient will be advised to inform their general practitioner of their trial participation, but this will not be a pre-requisite to enrolment. If the patient consents for their GP to be informed about participation (see Appendix 2) a letter should be sent to the GP (see Appendix 3).

Baseline assessments will be performed as listed below and as summarised in the Trial Schedule (see section 1.3).

- Review of medical and drug history since the screening visit
- Review of symptoms
- Review of concomitant medications
- Adherence to ART (patient will be asked about the number of missed doses in the previous 2 weeks, and in the previous 3 months)
- Targeted physical examination (as needed to evaluate symptoms; at this visit will include measurement of blood pressure, body weight, waist and hip-circumference, assessment of facial lipoatrophy and peripheral neuropathy)
- Neurocognitive assessment
- MOS-HIV quality of life questionnaire (self-completed by patient)
- EQ-5D health status questionnaire (self-completed by patient)
- Laboratory tests:
  - HIV viral load
  - CD4+ count
  - Full blood count (haemoglobin, white cells, neutrophils, lymphocytes and platelets)
  - Biochemistry (sodium, potassium, urea, creatinine, bilirubin, ALT, alkaline phosphatase)
  - Plasma storage (1 X 4ml EDTA tube)

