### **6.3.5 Strategy for stopping or interrupting treatment with PI monotherapy**

In addition to the virological rebound criteria given above, patients may be withdrawn (temporarily or permanently) from treatment with PI monotherapy for any of the following reasons at the discretion of the investigator:

- Disease progression while on therapy
- Unacceptable toxicity (e.g. insulin dependent diabetes developing *de novo*)
- Need for concomitant medication that has known interactions with the PI (and that cannot be avoided by switching to an alternative PI)
- Serious intercurrent illness or any change in the patient's condition which justifies the discontinuation or interruption of treatment in the clinician's opinion
- Pregnancy (a patient on monotherapy should be switched back to triple therapy for the duration of the pregnancy).
- Patient withdraws consent

PI monotherapy should be resumed as soon as possible, if considered clinically appropriate to do so (e.g. toxicity resolves, patient is no longer pregnant, or requirement for contraindicated concomitant medication ends).

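### Pregnancy is an exclusion at trial entry, but the only unconditional pregnancy test is at screening, up to 8 weeks earlier, so an unrecognised pregnancy can be randomised

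*Combined protocol and SAP*

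**What the plan says.** Criterion 7 in section 4.2 excludes a woman who is "Pregnant or trying to become pregnant at the time of trial entry". Section 5.1 requires every eligibility criterion to be met for entry.

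The screening laboratory list in section 4.3.2 includes "Urine (or serum) pregnancy test for women of childbearing potential". The pregnancy row of the trial schedule (section 1.3) is marked in the screening column only. Footnote 8 to that row adds that the test is "repeated at any subsequent visits where pregnancy is suspected".

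On timing, section 4.3.2 says "Potentially eligible individuals should be screened between 1 and 4 weeks before trial entry", and the schedule header gives screening as 4 weeks before Day 0 up to Day 0. Section 5.1 also sets 4 weeks as the aim, but then says "this may be extended to a maximum of 8 weeks for reasons of patient convenience or other operational reasons".

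The Day 0 list in section 5.1 contains an interval medical and drug history, a symptom review, viral load, CD4+ count, blood count, biochemistry and plasma storage. It contains no pregnancy test.

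For pregnancy arising during PI monotherapy, section 6.3.5 says that "a patient on monotherapy should be switched back to triple therapy for the duration of the pregnancy". The reason recorded in Appendix 14, where that wording was added, is the lack of data on whether PI monotherapy prevents mother-to-child transmission.

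**The concern.** The criterion is tied to one date and the routine evidence for it to another. Pregnancy status can change within weeks. The plan repeats viral load, CD4+ count, blood count and biochemistry at Day 0, but not the pregnancy test.

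A suspicion-triggered repeat cannot catch the case at issue, because an unrecognised pregnancy is by definition not suspected. Nothing in the Day 0 list prompts the suspicion specifically; it offers only general history and symptom review.

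What is at stake is verification of a stated entry criterion, and participant safety in the terms the protocol itself uses. Under section 6.3.1, a woman allocated to PI monotherapy stops her NRTIs immediately if she was on a PI-based regimen, or after 2 weeks if she was on an NNRTI-based one. The visits at Weeks 4, 8 and 12 carry no routine pregnancy test. She could therefore spend time on a regimen that the protocol says should be replaced during pregnancy.

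**Working it through.** **Reading the sections together**

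1. Date at which criterion 7 applies: trial entry (section 4.2).
2. Unconditional pregnancy tests: one, at screening (section 1.3 row; section 4.3.2 list).
3. Unconditional pregnancy tests at Day 0: none (section 1.3 row; section 5.1 list).
4. Conditional tests at Day 0: one, if pregnancy is suspected (footnote 8).
5. Age of the screening result at randomisation: 1 to 4 weeks as intended (section 4.3.2), at most 8 weeks, or 8 × 7 = 56 days (section 5.1).
6. Hence a suspected pregnancy at Day 0 should be tested for and would bar entry. One that is not suspected passes every listed check.

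**Size**

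The plan gives no figure for this, so there is none to reproduce. The sample size of 560 comes from section 9.3, and allocation is to equal arms (277 per arm before rounding up). Two inputs are assumptions that do not come from the documents: women make up 20% to 30% of participants, and they conceive at 3% to 6% per year.

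- Women randomised: 560 × 0.20 = 112 to 560 × 0.30 = 168.
- Conceptions in the gap = women × annual rate × weeks ÷ 52.
- Every gap 8 weeks, both arms: 112 × 0.03 × 8/52 = 0.52 to 168 × 0.06 × 8/52 = 1.55.
- Every gap 8 weeks, PI arm (half): 0.26 to 0.78.
- Every gap 4 weeks, both arms: 112 × 0.03 × 4/52 = 0.26 to 168 × 0.06 × 4/52 = 0.78.
- Every gap 4 weeks, PI arm (half): 0.13 to 0.39.

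For the assumed rates these lean high. They count all women rather than those of childbearing potential, they ignore that criterion 7 also excludes women trying to conceive, and they treat every such pregnancy as unsuspected. A Day 0 test would also miss the most recent conceptions, so it would not remove the whole of this number.

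**The case against.** The best defence is that the plan does check at Day 0. Footnote 8 covers that visit, history and symptoms are reviewed, all criteria must be met, and the trials unit checks eligibility before allocation (section 5.2). This stands against any reading that screening is the only point at which a test can be required. It does not close the gap, because each of these steps depends on someone suspecting pregnancy or on a result obtained at screening.

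A second defence is that section 5.1 confirms eligibility largely from screening evaluations, so a screening test with a triggered repeat is a legitimate choice and not a contradiction. It is indeed not a contradiction. But the viral load, CD4+ and fasting glucose criteria are written as values at screening, whereas criterion 7 is written as status at trial entry.

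Three stronger readings are tempting, and the documents do not support them:

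- **That a Day 0 test would prevent fetal drug exposure.** These women are already on triple therapy under section 4.1 and would remain on antiretrovirals if found ineligible. The protocol's recorded concern is prevention of transmission.
- **That the gap produces damaging early departures from the PI arm.** Section 6.3.5 treats pregnancy as a temporary interruption, with monotherapy resumed afterwards where appropriate. Section 9.5.1 analyses by intention to treat, and its sensitivity exclusion concerns early switches for personal preference, not clinical indication.
- **That nothing anywhere addresses pregnancy between the two visits.** The randomisation form is not reproduced, and the information sheet and consent form are not in the text reviewed, so this cannot be determined.

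It is also fair to say that pregnancy during follow-up is anticipated, both in management (section 6.3.5) and in reporting (section 11.4), and that 8 weeks is short beside 3 to 5 years of follow-up.

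**Conclusion.** The gap is real and small. As written, the plan lets a fully compliant site randomise a woman whose pregnancy began after screening and is not suspected, on a test result up to 8 weeks old. If she is allocated to PI monotherapy, her treatment is at odds with section 6.3.5 until the pregnancy is recognised.

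On the assumed rates the expected number in the PI arm is below one even if every gap were at the maximum. A reader might infer a threat to the trial's result; there is none, since the number is too small to have a material effect on power or the primary comparison. The point rests on verification and safety, and it deserves attention because it is so cheap to close. The conclusion that the gap exists depends only on the text; only its size depends on the assumed share of women and conception rate.

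The schedule header (4 weeks) and section 5.1 (8 weeks) also disagree on the screening window and need reconciling in their own right.

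**What to change.** Keep the screening test and add a repeat urine pregnancy test for women of childbearing potential to the Day 0 column of section 1.3 and the Day 0 list in section 5.1. Have the result read and entered on the randomisation form before it is faxed, so that the eligibility check in section 5.2 has a result from the day of entry. Repeating is better than moving the test: moving it would give up early detection and take a pregnant woman through the remaining screening procedures before she is excluded.

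Reconcile the schedule header with the maximum interval in section 5.1, and align footnote 8, which refers to women, with section 4.3.2, which refers to women of childbearing potential.

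The cost is one urine test per woman of childbearing potential and an occasional exclusion at Day 0 after screening has been completed. The change affects how an existing criterion is confirmed and alters no treatment rule.
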